### Intervention

This study is a multicentre clinical trial. To ensure the consistency and standardisation of treatment modalities across all clinical centres, therapists from the main centre conducted training sessions for therapists from the subcentres. The objective of these sessions was to standardise the Tuina treatment protocols and the TCE movement, and to treat patients in accordance with the interventions outlined in the study protocol. Prior to intervening with patients, therapists at subcentres must undergo training and evaluation at the main centre. They are not qualified to intervene until they have met the training requirements. Furthermore, to mitigate bias in the treatment of patients by different therapists, only one Tuina therapist and one TCE therapist were appointed to conduct the intervention at each clinical centre. TCE therapists must have at least 10 years of experience teaching TCEs.

To ensure that each subject can master the movement essentials of TCEs, a TCE treatment manual was issued to the subjects before the intervention. A comprehensive introduction to the movement essentials and precautions of TCEs through offline lectures and online video teaching mode followed. The therapist maintained a treatment log for each subject and recorded the subject’s progress and any issue that arise. If a subject has not completed the prescribed treatment within the allotted time, the therapist will contact the subject by phone to ensure that the subject has met the standard treatment volume.

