## Methods

### Study design

This study is a multicentre randomised controlled clinical trial study conducted in four clinical centres (Figure 1). The Wuxi Hospital of Traditional Chinese Medicine is the main centre. The Yueyang Hospital of Integrative Medicine affiliated with the Shanghai University of Traditional Chinese Medicine, Wuxi Rehabilitation Hospital and the Wuxi Xinwu District Hospital of Traditional Chinese Medicine are the three subcentres. Patients were recruited through advertisements at each centre. Patients who met the inclusion criteria were randomly assigned to either the TCE group or the Tuina combined with TCE group at a 1:1 ratio. The trial consisted of a four-week intervention period and subsequent three- and six-month follow-up periods. Data were collected before treatment, after 4 weeks of treatment, and at 3 months and 6 months of follow-up. The outcome assessment indicators included the Oswestry Disability Index (ODI), Short Form of Quality of Life (SF-36) Scale, Short-Form McGill Pain Questionnaire (SF-MPQ) Scale and gait analysis, which was used only for efficacy evaluations before and after 4 weeks of treatment.

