### Tuina with TCE group

The Tuina procedure was divided into localised muscle release and lumbar joint adjustment, and the whole process lasted for 20–30 min (Figure 3). The procedure started with gentle rubbing and kneading on both sides of the patient’s spine and buttocks using the fingertip surface for 10–15 min, and then pointing and pressing the local pain points or acupoints (e.g., BL23, BL24, BL25, BL40, and GB30) for 5 min. Following the completion of local muscle release, joint adjustments were performed utilising a lumbar blique-pulling manipulation and posterior lumbar extension. The lumbar blique-pulling manipulation was comparable with chiropractic manipulation (27), where an audible “click” indicated the successful completion of the procedure. Finally, lumbar back extension was performed. The patient was initially placed in the prone position, and the therapist pressed one hand on the patient’s spinal pain and slightly lifted the patient’s lower limbs with the other hand. The therapist then waited for the patient’s lumbar muscles to relax. Then, the therapist quickly lifted the patient’s lower limbs up to 30°–40° and then placed them down immediately. This maneuver can be done 3–5 times for about 5 min. Following Tuina, the patient should be permitted to rest in bed for approximately 10–15 min. The training movements and methods employed by the TCEs were identical to those utilised in the control group. Treatments were performed 3 times a week for 4 weeks.

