### Statistical analysis

The data will be subjected to analysis by our team of professional statisticians, who will employ IBM SPSS Statistics V.27.0 for this purpose. To assess the normality of the data, the Kolmogorov–Smirnov test was used. The quantitative results were expressed in terms of the mean and standard deviation. The purpose of the primary and secondary outcome indicators was to assess the difference in efficacy between the two groups. Hypothesis testing was employed to this end. The chi-square test was used to ascertain the dissimilarities in baseline data between the two groups. The analysis of variance for repeated measures was utilised to examine the alterations in efficacy between the two groups before, during and after the intervention, as well as after the follow-up period. For confounding factors that were challenging to regulate or were not regulated prior to treatment, such as an imbalance between the groups prior to treatment, were treated as covariates, and logistic regression was employed to ascertain the variability of efficacy between groups and to eliminate the influence of these factors on efficacy. The data collection and data summarisation were meticulously examined to minimise data anomalies. In the event of missing data, the data were assumed to be missing at random, and multiple interpolation would be employed for analysis. Subjects who were excluded from the trial will be excluded from the data set. The level of statistical significance was set at 5% (*p* < 0.05), and 95% confidence intervals were employed as effect estimates.

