## Discussion

Tuina and TCEs are an important part of Chinese traditional medicine with a history of thousands of years, playing an important role in protecting the health of the Chinese people and accumulating a great deal of clinical experience. Although multicentre clinical studies have been published on the use of Tuina combined with TCEs for the treatment of LDH (16), they have not performed long-term observations of efficacy, and the TCE manoeuvre lacks specificity. Standardised clinical randomised controlled trials to validate whether Tuina combined with TCEs is necessarily superior to single TCEs for relieving dysfunction and pain in patients with LDH are also lacking. Consequently, a multicentre, large-sample, assessor-blinded clinical randomised controlled trial was designed. The short- and long-term improvement of dysfunction and pain in LDH patients with Tuina combined with TCEs was assessed by evaluating the health status of the subjects through multiple outcome indicators at preintervention, after 4 weeks of intervention, and at the third and at sixth months’ follow-up to validate that the combination therapy is more advantageous than the treatment with single TCEs.

This study was conducted at multiple clinical centres, offering several advantages. Firstly, this study used four clinical centres, divided into one main centre and three subcentres. This structure facilitated more opportunities for subject recruitment and ensured an adequate sample size. Secondly, the results can be independently verified and repeated in each subcentre to confirm the consistency and reliability of the main results, thus reducing bias and increasing credibility. Thirdly, the observations focused on the recovery of dysfunction in patients with LDH, which was assessed using gait analysis to assist in evaluating the recovery of walking function in addition to the ODI scale. Additionally, a follow-up period of up to 6 months was conducted following the four-week intervention to facilitate observation of the short- and long-term efficacy of Tuina combined with TCEs for LDH.

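### The four Tuina operators coincide with the four centres, and the stated pooled analysis has no centre-specific estimate to support the claim that each subcentre can verify the result.

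*Protocol article*

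**What the plan says.** The Intervention section states that "only one Tuina therapist and one TCE therapist were appointed to conduct the intervention at each clinical centre". It gives the reason for this staffing rule in the same sentence: "to mitigate bias in the treatment of patients by different therapists, only one Tuina therapist and one TCE therapist were appointed". It also provides for standardisation between centres: "therapists at subcentres must undergo training and evaluation at the main centre", and nobody may treat before meeting the training requirements.

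Study design describes a "multicentre randomised controlled clinical trial study conducted in four clinical centres", with patients "randomly assigned to either the TCE group or the Tuina combined with TCE group at a 1:1 ratio". The section on the combined arm states that "The training movements and methods employed by the TCEs were identical to those utilised in the control group".

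Statistical analysis names the main method: "The analysis of variance for repeated measures was utilised to examine the alterations in efficacy between the two groups". Factors that were unregulated or imbalanced before treatment are to enter as covariates through a logistic regression. Neither centre nor therapist is mentioned.

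The Discussion lists as an advantage of the multicentre design that "the results can be independently verified and repeated in each subcentre to confirm the consistency and reliability of the main results".

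**The concern.** Four centres with one Tuina therapist each means four Tuina operators in the whole trial. Within a centre, every patient in the combined arm is treated by the same person, so operator skill and centre cannot be told apart. Because the exercises are the same in both arms, the Tuina operator is the therapist factor that sits in one arm only. Appointing one operator per centre deals with variation between therapists inside a centre. It does not deal with variation between the four operators, which is what a multicentre statement about Tuina depends on.

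The article then claims verification by subcentre, while the analysis it describes is a comparison of two pooled groups. If the effect were large with one or two operators and small with the others, the pooled result would not show it. The Discussion would still invite the reader to regard the effect as confirmed across centres. Leaving centre out also puts any between-centre difference in ODI into the error term, which costs precision.

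**Working it through.** **Inputs.** From Sample size calculation: means 14.53 and 19.73 (difference -5.2), SD 2.60, margin -4, two-sided alpha 0.05, beta 0.2, 74 per group, 166 in total, and a floor of 30 per group per centre. From Study design: four centres. Assumption: equal centres, so 166/8 = 20.75 per arm per centre.

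**The plan's own figure.** The distance from the margin is 5.2 - 4 = 1.2. With the denominator squared, n = 2 × (1.960 + 0.842)² × 2.60² / 1.2² = 73.7, that is 74 per group, as stated. At 83 per arm, SE = 2.60 × √(2/83) = 0.404 and power against the margin is Φ(1.2/0.404 - 1.96) = 84.5%. This is the pooled comparison, and it contains no centre or operator variance.

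**What one centre can show** (same inputs and normal approximation):

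| Patients per arm in the centre | SE = 2.60 × √(2/n) | 95% CI half-width = 1.96 × SE | Power against -4 = Φ(1.2/SE - 1.96) | Power against 0 = Φ(5.2/SE - 1.96) |
|---|---|---|---|---|
| 20.75 (equal centres) | 0.807 | 1.58 | Φ(-0.47) = 32% | Φ(4.48), above 99.9% |
| 30 (stated floor) | 0.671 | 1.32 | Φ(-0.17) = 43% | Φ(5.79), above 99.9% |

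If the plan's assumptions hold, a centre's interval will nearly always exclude zero. In most cases it will still include the margin of -4, because the half-width is larger than the 1.2 that separates the expected difference from the margin. The floor of 30 cannot be met in all four centres with 166 patients (4 × 2 × 30 = 240), so the second row can hold only for some centres. That mismatch is a separate matter.

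**Setting the statements side by side.** Intervention: operator equals centre. Statistical analysis: two groups, no centre. Discussion: each subcentre can verify the main result. The third statement needs centre-specific estimates, and the second does not provide them. Because centre identifies the Tuina operator, estimates by centre are also estimates by operator. The data needed are therefore already being collected, and what is missing is a stated analysis that uses them.

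**Which term does what.** A centre main effect (4 - 1 = 3 degrees of freedom) removes between-centre variation from the error term. On its own it does not show whether the treatment difference varies between centres. That needs the group-by-centre term (a further 3) or separate estimates. Neither can separate operator from centre.

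**The case against.** The best defence has four parts.

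- **A condensed article.** Centre adjustment is commonly left to the analysis plan, which is not shown, and the covariate sentence does not exclude centre. This stands against treating the missing centre term alone as an error. It does not answer the mismatch, since the article itself claims verification by subcentre and describes an analysis that does not deliver it.
- **The staffing rule is sensible.** One operator per centre does reduce variation within a centre, and training and evaluation at the main centre address differences between centres. This stands. The rule is incomplete as a safeguard, but it does not work against its own purpose.
- **The comparison is protected.** A reader might infer that the Tuina effect is biased or that operator effects are hidden beyond recovery. The documents do not support this. Patients are randomised individually, the TCE component is the same in both arms, and general centre effects balance in expectation. Centre identifies the operator, so operator-specific results can be shown.
- **Consistency is not superiority in every centre.** A reader might infer that each subcentre must clear the -4 margin, which all three would do with probability of about 0.318³ = 3% at 20.75 per arm. The Discussion sets no such criterion, and against zero each centre is amply powered. The 32% and 43% therefore describe the margin only.

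A further tempting reading is that ignoring operators inflates the type I error. If operators accounted for 2% to 10% of ODI variance in the combined arm (an assumed range with no source in the documents), the design effect in that arm would be 1 + 19.75 × ICC = 1.40 to 2.98. The variance of the difference would rise by (1 + 1.40)/2 = 1.20 to (1 + 2.98)/2 = 1.99. A nominal 5% test would then have an error of 2 × (1 - Φ(1.96/√1.20)) = 7% to 2 × (1 - Φ(1.96/√1.99)) = 16%. This applies only to conclusions about Tuina operators in general, and a fixed centre term would not cure it. It is an illustration and not part of the finding.

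**Conclusion.** The point holds in a limited form, as a change that should be made. Tuina operator and centre are the same factor, the staffing rule addresses variation within centres only, and the Discussion claims a by-centre check that the stated pooled analysis does not include. The between-group comparison is valid for these four operators. The loss lies in precision, in the evidence for consistency across centres, and in how far the result extends to other operators.

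On the plan's SD and means, one centre has about 32% power against the -4 margin under equal centres, 43% at 30 per arm, and close to 100% against zero. These figures rest on the plan's SD of 2.60 and true difference of -5.2, with the 4-week ODI as in its sample size calculation. The size of any real operator effect cannot be judged from the document.

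**What to change.** 1. **Statistical analysis:** include centre as a fixed factor in the primary ODI model.
2. **Statistical analysis:** pre-specify the group-by-centre term as a descriptive consistency analysis. Report the ODI difference with 95% CI for each centre, and note that operator and centre cannot be separated.
3. **Intervention:** say that one therapist per modality per centre limits variation within a centre only.
4. **Discussion:** replace the claim of independent verification with a description of the centre-specific estimates, and note that only four Tuina operators were studied.

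If the full analysis plan already contains items 1 and 2, the article needs only to say so and to make the two wording changes.

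The cost is three degrees of freedom for centre, three for the interaction, and a weaker replication claim. Centre is known for every patient, so neither the design nor the data collection changes.

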### TCE group

The TCE group comprised four movements, selected from Baduanjin, Taiji and Wuqinxi, with minor modifications to accommodate the patients’ varying learning and exercise abilities. The program primarily encompassed the fourth movement of Baduanjin, the Yunshou of Taiji, Huju and Luben from Wuqinxi. All movements were supervised by qualified TCE instructors. Firstly, patients performed warm-up exercises for about 5 min to avoid muscle strain during exercise. Then, the TCEs were performed in the order of A–D (Figure 2), and each movement was repeated 3 times, with 4 movements as 1 set, for a total of 2 sets of exercise, which should last 15 min or more. Finally, a 5-min stretching exercise was performed. Treatments were performed 3 times a week for 4 weeks.

**Figure 2 fig2:**
[figure not shown]
Schematic diagram of the movements of the four TCEs. **(A)** Fourth movement of Baduanjin, **(B)** Yunshou **(C)** Huju, **(D)** Luben. **(D2–D5)** Demonstrates the movements from the side. Each movement alternates between the left and right sides or the up and down directions, and the entire sequence is continuous. Each movement is repeated three times, and four movements are performed as a set for a total of two training sets.

### Tuina with TCE group

The Tuina procedure was divided into localised muscle release and lumbar joint adjustment, and the whole process lasted for 20–30 min (Figure 3). The procedure started with gentle rubbing and kneading on both sides of the patient’s spine and buttocks using the fingertip surface for 10–15 min, and then pointing and pressing the local pain points or acupoints (e.g., BL23, BL24, BL25, BL40, and GB30) for 5 min. Following the completion of local muscle release, joint adjustments were performed utilising a lumbar blique-pulling manipulation and posterior lumbar extension. The lumbar blique-pulling manipulation was comparable with chiropractic manipulation (27), where an audible “click” indicated the successful completion of the procedure. Finally, lumbar back extension was performed. The patient was initially placed in the prone position, and the therapist pressed one hand on the patient’s spinal pain and slightly lifted the patient’s lower limbs with the other hand. The therapist then waited for the patient’s lumbar muscles to relax. Then, the therapist quickly lifted the patient’s lower limbs up to 30°–40° and then placed them down immediately. This maneuver can be done 3–5 times for about 5 min. Following Tuina, the patient should be permitted to rest in bed for approximately 10–15 min. The training movements and methods employed by the TCEs were identical to those utilised in the control group. Treatments were performed 3 times a week for 4 weeks.

**Figure 3 fig3:**
[figure not shown]
Tuina operation method. **(A–C)** Localised muscle release. **(D,E)** Lumbar joint adjustments. **(A)** Press and wipe. **(B)** Pressure and kneading. **(C)** Pressing on pain points or acupoints. **(D)** Lumbar blique-pulling manipulation. **(E)** Posterior lumbar extension.

### Outcomes

The efficacy evaluation in this study concentrated on the primary outcome indicator, namely the recovery of dysfunction in patients before, after and during the follow-up period. In addition, several secondary indicators were evaluated, including quality of life, pain and gait analysis. The data collection at each time point was conducted by independent researchers who were not privy to the specific subgroups and were not involved in other aspects of the study. The specific time points for data collection are presented in Figure 4.

**Figure 4 fig4:**
[figure not shown]
Enrolment, pre- and post-intervention, and follow-up data collection schedules.

### Primary outcome

The ODI scale, which consists of 10 items in 3 dimensions, namely pain, individual functioning and overall personal functioning, was used as a comparison of efficacy before and after treatment and between groups (28). The maximum score was 50; the higher the score, the higher the degree of dysfunction of the patients.

### Secondary outcome

The SF-36 Scale evaluates health in eight dimensions, including physical functioning, general mental health and social functioning, and higher scores indicate better health (29). Each dimension was rated with a maximum of 100 points and a minimum of 0 points.

The SF-MPQ Scale includes three parts: pain rating index (PRI), (VAS) and present pain intensity (PPI) (30). The PRI assesses the patient’s emotional and sensual experiences of pain. The VAS provides a straightforward visual representation of the patient’s pain level. The PPI determines the intensity of the patient’s current pain on a six-point scale (0–5).

Gait analysis is the process of collecting patient information using a wearable 3D gait analyser. Gait analysis encompasses a range of patient data, including step length, cadence, stride length and double support phase. This information is utilised to assess the patient’s motor function and musculoskeletal rehabilitation status (31).

After all the relevant items were confirmed by the patients themselves, the total score reflecting the degree of low back and leg pain in each period was calculated cumulatively by a specialised statistician, and the results were used for pre- and post-treatment comparisons as well as comparisons between groups.

### Adverse events

The treatment responses of all patients with lumbar intervertebral disc herniation who received Tuina in conjunction with TCEs were monitored and documented throughout the course of the study. Adverse events during the treatment period were recorded and analysed to ascertain whether it was related to the treatment. Adverse events included those that occurred during the clinical trial and resulted in hospitalisation, prolonged hospitalisation, disability, impairment of the ability to work, life-threatening injury or death. In case of any serious adverse event, whether related to the intervention, the trial should be terminated immediately and appropriate rescue treatment initiated without delay. Such incidents must also be reported within 24 h to the responsible unit, the ethics committee, the sponsoring organisation and the relevant personnel of the drug regulatory authority. The relevant information must be recorded in the case file.

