**Methods/design:**

The design is a multicentre, assessor-blinded clinical randomised controlled trial. A total of 166 patients with LDH (aged 18–65 years) were recruited from four centres and randomly assigned at a 1:1 ratio to two groups: the TCE group and the Tuina combined with the TCE group. Each group received three treatments over the course of 1 week for a total of 4 weeks. The primary outcome indicator was the Oswestry Disability Index, whereas the secondary outcome indicators were the Short Form of Quality of Life Scale, the Short-Form McGill Pain Questionnaire Scale, and gait analysis. Assessments were made before the treatment, at the end of the treatment, and at the third and sixth months’ follow-ups. Gait analysis was only used for comparison between the two groups before and after treatment, and did not involve follow-up. Adverse events occurring during the trial were faithfully recorded.

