**Conclusion:**

The results of this study are expected to provide a more effective research protocol for symptomatic LDH and an evidence-based rationale for the efficacy and safety of Tuina combined with TCEs in the treatment of symptomatic LDH.

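### The Adverse events section does not separate adverse from serious adverse events, names only the Tuina+TCE arm for monitoring, and gives conflicting recording periods

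*Protocol article*

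**What the plan says.** The Adverse events section makes four statements that bear on this point.

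- **Who is monitored:** treatment responses of patients "who received Tuina in conjunction with TCEs were monitored and documented throughout the course of the study".
- **When events are recorded:** "Adverse events during the treatment period were recorded and analysed to ascertain whether it was related to the treatment".
- **What counts as an adverse event:** "Adverse events included those that occurred during the clinical trial and resulted in hospitalisation, prolonged hospitalisation, disability, impairment of the ability to work", followed by life-threatening injury or death.
- **What follows from a serious adverse event:** termination and reporting within 24 hours. No criteria distinguish this term from the one just described.

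Elsewhere, the abstract (Methods/design) says "Adverse events occurring during the trial were faithfully recorded", with no arm named. Study design gives the timeline: "The trial consisted of a four-week intervention period and subsequent three- and six-month follow-up periods". The Intervention section has the therapist keep a treatment log for each subject that notes progress and any problem.

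Safety is a stated aim. The abstract's conclusion expects "an evidence-based rationale for the efficacy and safety of Tuina combined with TCEs in the treatment of symptomatic LDH". The Sample size calculation section gives full evaluation of efficacy and safety as a reason for planning 166 cases, and the Discussion promises evidence on safety.

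**The concern.** Tuina is the only planned difference between the arms, and it includes joint manipulation. Any harm it adds can be seen only by comparing the two arms, with events defined and sought in the same way in each.

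The text departs from that in three ways. Soreness or a short-lived rise in pain after manipulation has no stated place in the definition. The monitoring sentence mentions one arm, in a trial where patients know their allocation, so events may be sought harder in that arm. The period over which events count is not fixed. A site that followed the section literally could record few or no events, or more in one arm because more were looked for. Neither result would say how safe the added component is.

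The blurred terms matter for a second reason. Termination and rapid reporting hang on a category that the section does not separate from adverse events in general.

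**Working it through.** The plan gives no safety figure to reproduce, so the main check is to set the statements side by side.

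**Definition.** Hospitalisation, prolonged hospitalisation, disability, life-threatening injury and death are seriousness outcomes. Impaired ability to work is the loosest item: it could admit a pain flare that keeps a patient from work, but not one that does not. The verb *included* leaves room for other events, yet no wider category appears anywhere in the article.

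**Arm.**

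| Place | Subject | Arm named |
|---|---|---|
| Adverse events, monitoring sentence | treatment responses | Tuina with TCEs only |
| Adverse events, recording sentence | adverse events | none |
| Abstract, Methods/design | adverse events | none |
| Intervention | log of progress and problems | every subject |

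**Period.**

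| Place | Period |
|---|---|
| Adverse events, monitoring sentence | whole course of the study |
| Adverse events, recording sentence | treatment period |
| Adverse events, definition | clinical trial |
| Abstract, Methods/design | trial |

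Three statements point to the whole trial and one to treatment only.

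**Scale of the conflict over the period.** Treatment lasts 4 weeks. If month 6 is counted from baseline, observation lasts about 26 weeks and 4/26 = 15%. If it is counted from the end of treatment, observation lasts about 30 weeks and 4/30 = 13%. This share applies only if the treatment-period sentence is the rule that sites follow.

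**Scale of the arm issue.** With 1:1 allocation of 166, each arm has 166/2 = 83 patients. The monitoring sentence names one arm and is silent on the other 83.

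**What the definition decides (illustration; all event rates below are assumptions).**

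- Serious events: the chance of at least one event in 83 patients is 1 − (1 − p)^83. This gives 8% at p = 0.1%, 34% at p = 0.5% and 57% at p = 1%.
- With zero events in 83, the one-sided 95% upper limit is 1 − 0.05^(1/83) = 3.5%. This limit comes from arm size alone and would be the same after the fix, so it does not measure the defect.
- Commoner, non-serious events: power = Φ{[|p1 − p2| − 1.96·√(2p̄(1 − p̄)/n)] / √[(p1(1 − p1) + p2(1 − p2))/n]}, with n = 83 and p̄ the mean of the two rates.
  - For 5% against 20%: (0.150 − 1.96 × 0.0513)/0.0500 = 0.99, so power is 84%.
  - For 10% against 20%: (0.100 − 1.96 × 0.0554)/0.0549 = −0.16, so power is 44%.

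A trial of this size can say something about common non-serious harms and little about rare serious ones. The present definition describes only the second kind.

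**The case against.** The strongest reply is that the section is loosely worded and not restrictive.

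- *Period.* A reader might infer that recording stops at the end of treatment. The documents do not support that: the abstract and two sentences of the section itself refer to the whole trial. All manipulation also falls within the 4 treatment weeks, so the time share overstates what a short window would lose.
- *Arm.* A reader might infer that TCE-only patients go unrecorded. No sentence says so. The sentence that names one arm concerns treatment responses, the recording sentences name no arm, and the therapist's log covers every subject.
- *Definition.* The verb *included* is not exclusive, and the separate use of serious adverse event suggests that two tiers were intended. Worsening pain or function is also captured in both arms by the SF-MPQ and ODI at every assessment, though not as adverse events.
- *Status of safety.* Safety is not a listed primary or secondary outcome, and the article does not claim that the combination is safer than TCE alone.
- *Condensation.* The full protocol and the case record form are not shown and may define events more widely. Severity grading, relatedness scales and interval estimates are commonly left to them.

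Most of this stands, and it limits the point to what the text states. It does not remove the point. If two tiers were intended, the section gives criteria for only one. The log is a treatment log that does not use the term adverse event, and nothing links it to the adverse-event analysis. Four period statements that disagree are a contradiction in the text, not a detail left out of it.

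**Conclusion.** The point holds as a defect of stated rules. The section describes adverse events only by serious-outcome criteria, does not separate them from serious adverse events, names one arm for monitoring and gives inconsistent periods. Followed literally, it does not support a comparative safety statement, although the article presents safety as an aim in the abstract, the sample size section and the Discussion.

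A reader might go further and conclude that the trial cannot support any safety conclusion. That would follow only if every ambiguity were resolved in the narrowest way and the unseen case record form were no wider. The documents do not establish either.

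The size of the effect on the safety results cannot be calculated. The figures for 83 patients and 13% to 15% of observation time mark how far the ambiguity reaches if the narrow readings were applied. They are not estimates of lost events. The ODI comparison is not affected.

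**What to change.** Rewrite the Adverse events section so that:

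1. an adverse event is any untoward event, serious or not;
2. events are sought and recorded in the same way in both arms;
3. one period is stated, from randomisation to month 6, and the abstract agrees with it;
4. serious events are a defined subset, marked by a separate flag, so that the termination and reporting sentence refers to a defined term. What those consequences should be is for the sponsor to reconcile;
5. the number and percentage of patients with events are reported by arm.

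The cost is one paragraph and a few fields on the uniform case record form, with slightly more recording by site staff and no extra visits. Because an answer about events may reveal allocation, the blinded evaluator should complete the outcome scales first, or another person should ask.

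Recruitment and treatment are described largely in the past tense. For patients already treated, the treatment logs can be searched in both arms, but non-serious events not recorded at the time cannot be fully recovered. The report should state this as a limitation.
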